### Aims and hypotheses

1.1

This study aims to compare suicide risk estimates across different populations and conditions. Specifically, the objectives are: (i) to compare suicide risk evaluations across the different study groups; (ii) to examine the temporal stability of suicide risk estimates when participants evaluate different but comparable clinical scenarios over time; and (iii) to assess whether the use of a structured instrument (C-SSRS) is associated with greater convergence in risk classification compared to unstructured judgment based on personal or clinical impressions. In addition to group-based comparisons, the study will examine whether differences are better explained by dimensional indicators of clinical experience rather than by professional labels alone.

Additionally, based on the expected results, the following hypotheses were formulated:

*HP 1*: Greater clinical experience and prior exposure to suicide-specific training will be associated with higher agreement and more consistent suicide risk estimates, regardless of professional category (Aim 1).

*HP 2*: Differences in risk estimation are expected to reflect variability in clinical exposure to acute suicidal presentations rather than disciplinary background per se (Aim 1).

*HP 3*: All study groups will show lower agreement for intermediate risk categories compared to low and high-risk categories (Aim 1 and 2).

*HP 4*: Greater within-subject variability is expected among individuals with limited or no clinical exposure to suicidal behavior compared to those with greater prior clinical exposure. This expectation is based on the idea that personal experiences, momentary emotional states, and situational cues may exert a stronger influence on individuals who are not familiar with clinical decision-making, whereas healthcare professionals are trained to rely primarily on clinical information and data (Aim 2).

*HP 5*: Participants assigned to the experimental condition (brief training on suicide risk assessment and use of the C-SSRS) will exhibit greater between-subjects and within-subject agreement in suicide risk estimates across all study groups (Aim 3).

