**Figure 2 f2:**
[figure not shown]
Conceptual framework of the CARE study showing the baseline and follow-up assessments.

The questionnaire will be designed so that each participant will be randomly assigned to 6 different vignettes to be evaluated, 2 for each risk category (low, moderate, and high). Specifically, participants assigned to the C-SSRS condition will complete a brief training module on basic suicidology notions embedded within the online questionnaire before evaluating the vignettes. The module is delivered as a single self-administered page and requires approximately 5 minutes to be completed. It is divided into two sections: first, it will provide concise definitions of suicide-related constructs, including thoughts of death, suicidal ideation, suicidal planning, non-suicidal self-injury, suicide attempt, and suicide death, in order to reduce interpretative variability across respondents; second, it will present step-by-step instructions on how to use the C-SSRS (14), explaining the logic of the six screening questions, when conditional questions are administered, and how responses map onto the three risk categories defined by the scale (low, moderate, high). Ultimately, participants will be provided with access to the official Italian version of the C-SSRS and informed that a mobile application version can be used if preferred. No feedback, supervision, or competency assessment will be provided, thereby reflecting the type of brief orientation often available in real-world implementation settings. The remaining participants will be asked to provide a subjective estimation of perceived suicide risk based on their impressions, knowledge, personal judgment, or clinical experience (for clinicians). Notably, for participants without a clinical background, the task is framed as an estimation of perceived suicide risk rather than a diagnostic or clinical evaluation. They will not be required to make clinical decisions but are instead asked to describe how they would interpret and respond to the situation described in the vignette. Participants assigned to the C-SSRS condition will be instructed, for each vignette, to provide a categorical rating of suicide risk as defined by the scale (low, moderate, high); whereas those assigned to the No-C-SSRS condition will be asked, for each vignette, to provide an ordinal risk estimate on a scale from 1 (very low risk) to 9 (imminent risk). Notably, the use of different response formats across conditions reflects the distinct decision-making frameworks under investigation. The C-SSRS operationalizes suicide risk through predefined categorical classifications and does not provide a continuous scoring system, while a 1–9 ordinal scoring metric will be adopted for the No-C-SSRS condition to better capture the natural variability of subjective risk appraisal without imposing a fixed, limited categorization. This approach allows the study to compare two ecologically valid assessment paradigms, structured categorical evaluation versus dimensional judgment, rather than two versions of the same measurement model.

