#### Follow-up assessment

2.3.2

Two weeks after completing the baseline questionnaire, each participant will receive an email reminder to complete the follow-up questionnaire. The follow-up assessment will require participants to evaluate 6 vignettes (2 per risk category), randomly selected from the same pool of 18 vignettes, to examine consistency between baseline and follow-up ratings. Notably, different vignettes are intentionally administered at follow-up to avoid recall effects and to evaluate the temporal stability of participants’ general risk estimation approach rather than agreement on identical cases. Participants assigned to the C-SSRS condition at baseline will again be asked to provide a categorical rating of suicide risk as defined by the C-SSRS (low, moderate, high), although no informational training will be provided at follow-up. Concurrently, participants in the No-C-SSRS condition will be asked, for each vignette, to provide an ordinal suicide risk rating from 1 (very low risk) to 9 (imminent risk), following the same procedure used at baseline. If participants do not complete the follow-up questionnaire within five days of receiving the first reminder, up to three additional reminders will be sent, each one three to five days apart.

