To quantify inter-rater agreement across raters for each vignette, Krippendorff’s alpha will be used as the primary agreement index, as it is appropriate for multi-rater settings with potentially unbalanced data. Weighted kappa coefficients will be computed only in supplementary pairwise comparisons to facilitate interpretability relative to commonly reported agreement metrics. Within-person analyses will evaluate the stability of participants’ overall level and pattern of risk estimates across time using different vignette sets drawn from the same risk-calibrated pool. These analyses do not represent test–retest reliability of identical stimuli but rather the temporal consistency of risk perception. Because different vignettes of the same risk category will be administered at baseline and follow-up, within-person analyses will be conducted on participant-level summary indices (e.g., central tendency of ratings and distribution of risk categories across vignettes at each time point) rather than on vignette-level paired comparisons. For the No-C-SSRS condition, paired non-parametric tests, such as the Wilcoxon signed-rank test, and correlation analyses will be used. For the C-SSRS condition, indices of temporal consistency will be computed to evaluate the stability of participants’ overall tendency to classify scenarios into risk categories across time, rather than agreement on identical stimuli.

The mixed-effects framework described above will also be used to examine interaction effects. Pre-specified interaction terms will examine whether differences in risk estimation vary as a function of demographic and professional variables (e.g., age, gender, years of clinical experience, prior suicide-specific training) across study group and experimental condition. In addition, to control for inflation of Type I error due to multiple comparisons, p-values from secondary analyses will be adjusted using the false discovery rate approach.

Missing data will be handled under a missing-at-random assumption using maximum likelihood estimation within mixed-effects models, which allows inclusion of all available observations without listwise deletion. Attrition between baseline and follow-up will be examined descriptively, and sensitivity analyses will compare participants who completed follow-up with those who did not. Predictors of attrition will be explored to assess potential systematic differences between completers and non-completers.

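### In the No-C-SSRS arm the named paired tests detect only mean drift, and no named analysis compares within-person variability for HP 4 or on a common scale for HP 5

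*Protocol article*

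**What the plan says.** Section 2.4.2 puts the stability of each person's risk appraisal over time into the primary outcome. In section 1.1, HP 4 is a statement about spread: "Greater within-subject variability is expected among individuals with limited or no clinical exposure to suicidal behavior". HP 5 adds that within-subject agreement should be greater in the C-SSRS condition.

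Baseline gives each person two vignettes per risk category (section 2.3.1). At follow-up (section 2.3.2) participants "evaluate 6 vignettes (2 per risk category), randomly selected from the same pool of 18 vignettes", and the vignettes are meant to differ from those seen at baseline.

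Section 2.5.2 sets the target: "Within-person analyses will evaluate the stability of participants’ overall level and pattern of risk estimates across time using different vignette sets". It then fixes the unit of analysis: "within-person analyses will be conducted on participant-level summary indices (e.g., central tendency of ratings and distribution of risk categories across vignettes at each time point"). For the 1–9 ratings the methods are: "For the No-C-SSRS condition, paired non-parametric tests, such as the Wilcoxon signed-rank test, and correlation analyses will be used". The C-SSRS arm gets separate, unnamed indices of consistency.

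The same section makes mixed-effects models the primary approach. They have random intercepts for participants, vignette intercepts where judged appropriate, and fixed effects for group, condition, time and their interactions.

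**The concern.** The named methods do not match the question in three ways.

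1. A paired location test looks at the centre of the change distribution. Instability widens that distribution without moving its centre.
2. The summaries come from different random vignettes at each visit. A perfectly consistent rater can change score because the cases changed.
3. HP 4 and the within-subject part of HP 5 compare variability between kinds of people or between conditions. Neither a paired test nor a correlation, as described, makes that comparison.

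At stake are the within-subject half of the primary outcome, HP 4, and part of HP 5. The study could report a mean-drift test and correlations of unknown attenuation, and still have no test of the hypotheses it states.

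**Working it through.** **Inputs from the protocol.** Section 2.5.1 plans 500 participants with 40% to 45% attrition: 500 × 0.55 = 275 and 500 × 0.60 = 300, which reproduces its follow-up range. Half of that is 137.5 to 150 per condition; 140 is used here. There are 18 vignettes, two per category at each visit. The protocol gives no figure for the stability analysis itself.

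**Assumptions, not in the protocol.** Six vignettes per category (18/3), none repeated for a participant; category means 2.5, 5 and 7.5; between-person SD σ_p = 0.8; residual SD σ_e = 1.0; within-category vignette SD σ_v from 0 to 1.5; person-by-time SD σ_pt of 0 (stable), 0.8 or 1.5 (unstable). Ratings are rounded to 1–9, the summary is the mean of six ratings, and each setting has 1,000 simulated data sets.

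**Step 1: what each named method responds to (σ_v = 0.5).**

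| Raters | Wilcoxon rejects | Spearman rho | Mean absolute change |
|---|---|---|---|
| Stable | 4.6% | 0.71 | 0.50 |
| Unstable, σ_pt = 0.8 | 3.6% | 0.40 | 0.94 |
| Unstable, σ_pt = 1.5 | 6.1% | 0.19 | 1.5 |
| Stable, all shift by 0.3 | 99.9% | 0.71 | 0.54 |
| Stable, all shift by 0.5 | 100% | 0.71 | 0.62 |

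Wilcoxon reacts to drift and not to instability. The correlation does the reverse.

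**Step 2: vignette differences in the correlation.** Drawing two of six vignettes without replacement gives a category mean with variance σ_v²/3, so σ_v²/9 after averaging three categories. A non-overlapping follow-up set adds a covariance of −σ_v²/18. Before rounding, the expected correlation of the two participant means is

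r = (σ_p² − σ_v²/18) / (σ_p² + σ_pt² + σ_v²/9 + σ_e²/6).

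For fully stable raters (σ_pt = 0):

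| σ_v | Formula | Simulated rho, unadjusted | Simulated rho, vignette-centred |
|---|---|---|---|
| 0 | 0.640/0.807 = 0.79 | 0.756 | 0.755 |
| 0.5 | 0.626/0.834 = 0.75 | 0.712 | 0.754 |
| 1.0 | 0.584/0.918 = 0.64 | 0.596 | 0.747 |
| 1.5 | 0.515/1.057 = 0.49 | 0.441 | 0.735 |

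Rank correlation on rounded, truncated ratings runs slightly below the formula; the pattern is the same. Stable raters at σ_v = 1.5 (0.44) look like unstable raters (σ_pt = 0.8) with no vignette variance (0.42). Unadjusted mean absolute change for stable raters rises from 0.45 to 0.74 as σ_v goes from 0 to 1.5. After centring it stays near 0.44, against 0.86 to 0.92 for unstable raters (σ_pt = 0.8).

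**Step 3: comparability across groups.** Take equally stable raters from a more homogeneous group, σ_p = 0.3 with σ_v = 0.5: r = (0.090 − 0.014)/(0.090 + 0.028 + 0.167) = 0.076/0.285 = 0.27, simulated rho 0.24. With σ_p = 0.8 the values are 0.75 and 0.71. The correlation differs although stability does not.

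**Step 4: hypotheses against methods.** HP 4 needs within-person variability compared by clinical exposure. The paired test gives a mean change, the correlation mixes stability with spread, and the mixed model's time effect and interactions concern the level of ratings. Its random effects are intercepts only, with no participant-by-time term and no group-specific variance. HP 5 needs one within-subject index in both conditions, but section 2.5.2 gives the 1–9 arm one set of methods and the three-category arm another.

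**The case against.** The strongest defence is that the two named methods are complementary: a paired test addresses level and a correlation addresses rank order, which fits the stated target of level and pattern. This stands as far as it goes. A reader might infer that both methods see only drift. The protocol names the correlation alongside the paired test, and Step 1 shows that it falls clearly with instability and ignores drift.

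A reader might also infer that the investigators will read non-significance as stability, or that raw means are certain to be used. The protocol says neither. Its examples of indices and tests are open lists, and the absence of vignette adjustment is inferred from silence in a condensed article. Still, other paired location tests share Wilcoxon's property, so the open list does not help on that point.

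The design also limits the vignette problem. Two vignettes per category at each visit balance difficulty between categories, and random allocation means vignette noise should dilute group comparisons rather than favour a group. The protocol discloses that stimuli differ: "These analyses do not represent test–retest reliability of identical stimuli but rather the temporal consistency of risk perception". These points reduce the mixing but do not remove differences within a category. The planned mixed model already contains much of what is needed. What it lacks is a within-person variability term and a firm commitment to vignette intercepts.

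**Conclusion.** The point holds in a limited form.

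- **Firm, and independent of the assumed variances:** the paired tests named for the No-C-SSRS arm address mean drift only, so a null result does not show stability. No named analysis compares within-person variability by exposure for HP 4. The two conditions have no common within-subject index for HP 5.
- **Dependent on assumptions:** how far vignette differences attenuate the correlation. The within-category vignette SD is not in the protocol. The loss is small at 0.5 (0.76 to 0.71) and material at 1.0 or more (0.60, then 0.44 at 1.5). It also presumes that the summaries are not adjusted for vignette.
- **Not supported:** that the correlation is blind to instability.

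This should be settled before follow-up data are analysed.

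**What to change.** 1. Keep Wilcoxon, labelled as a test of mean drift only.
2. Estimate stability from the planned ordinal mixed model, always including vignette random intercepts and adding a participant-by-time random effect. Report the stability ICC, σ_p²/(σ_p² + σ_pt²), with its interval. Vignette-centred participant means can serve as the simpler or sensitivity version, since they treat the scale as continuous and section 2.5.2 reserves that for sensitivity analyses.
3. For HP 4, compare the participant-by-time variance, or the absolute change in vignette-adjusted participant level, across exposure and study group within each condition.
4. For the within-subject part of HP 5, compare conditions on the three-category metric of Table 1, because absolute changes on a 1–9 scale and on three categories are not comparable.

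The cost is plan wording and modest extra modelling on data already being collected. Variance estimates will be imprecise in small groups: with equal allocation, 275/20 to 300/20 gives about 14 to 15 completers per group and condition. The comparison by exposure is therefore likely to be more informative than ten separate group estimates.

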#### Baseline assessment

2.3.1

The study procedures and enrollment process are shown in **Figure 2**. During the baseline assessment, participants will be asked to answer sociodemographic questions as well as to indicate their professional and academic background, in order to assign them to a specific study group. Then, participants of each group (i–x) will be randomly assigned to one of the two conditions (C-SSRS *vs.* No-C-SSRS).

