#### Outcomes

2.4.2

The primary outcome will be the assessment of discrepancies in suicide risk estimates across study groups (between-subjects) and the evaluation of the stability of individual risk appraisal tendencies over time (within-subject), in order to identify specific patterns and factors that may influence variability and inter-rater agreement in risk estimation across different clinical scenarios.

The secondary outcome is the assessment of discrepancies in suicide risk estimates between the C-SSRS and No-C-SSRS conditions, in order to determine whether the use of a standardized suicide risk assessment instrument will lead to greater homogeneity in risk ratings across the study groups. To allow comparison of discrepancies between the two subgroups, suicide risk assessment will be expressed as categorical variables for participants assigned to the C-SSRS condition (low, moderate, high) and as ordinal scores for participants in the No-C-SSRS condition (from 1 to 9). Cut points were defined *a priori* to represent three clinically interpretable categories of risk intensity, corresponding to low (scores 1-3), intermediate (4–6), and high (7–9) perceived risk. This mirrors the three-level structure imposed by the C-SSRS while preserving the ordinal distribution of the original ratings (**Table 1**).

**Table 1 T1:** Conversion of the suicide risk estimates between the C-SSRS and No-C-SSRS conditions.

C-SSRS condition risk categories	No-C-SSRS condition risk scores
Low risk	1-2–3 scores
Moderate risk	4-5–6 scores
High risk	7-8–9 scores

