#### Planned statistical analysis

2.5.2

Analyses will examine discrepancies in suicide risk assessment across participant groups and over time to identify factors associated with variability. Descriptive statistics will summarize sociodemographic and professional characteristics of the sample, distribution of risk ratings, and follow-up completion rates. Given the hierarchical structure of the data, with multiple vignette ratings nested within participants, mixed-effects regression models will constitute the primary analytical approach. Random intercepts will be specified for participants to account for repeated ratings within individuals and, when appropriate, for vignettes to account for shared variance attributable to scenario characteristics. Fixed effects will include study group, experimental condition (C-SSRS vs. No-C-SSRS), time (baseline vs. follow-up), and their interactions.

Ratings collected on the 1 to 9 scale will be treated as ordinal variables. Accordingly, ordinal mixed-effects models will be used as the primary approach, whereas linear models treating the scale as continuous will be conducted only as sensitivity analyses to ensure robustness of findings. To evaluate potential bias related to categorization thresholds, sensitivity analyses will include alternative binning strategies (e.g., 1–2 vs. 3–7 vs. 8–9) and models using the full 1–9 scale without categorization.

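### The within-subject clause of HP5 compares the randomised arms, but section 2.5.2 analyses within-person stability separately by arm with non-comparable statistics, and the only between-arm contrast over time tests average level, not individual consistency

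*Protocol article*

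**What the plan says.** All references are to the protocol article.

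- **Hypothesis (1.1, Aims and hypotheses).** HP5 states that participants in the experimental condition "will exhibit greater between-subjects and within-subject agreement in suicide risk estimates across all study groups (Aim 3").
- **Randomisation (2.3.1, Baseline assessment).** After sorting into study groups, "participants of each group (i–x) will be randomly assigned to one of the two conditions".
- **Secondary outcome (2.4.2, Outcomes).** The question between conditions is whether the instrument "will lead to greater homogeneity in risk ratings across the study groups". Table 1 maps 1–3, 4–6 and 7–9 to low, moderate and high so that the two conditions can be compared. Within-person consistency by condition is not named here.
- **Within-person analysis (2.5.2, Planned statistical analysis).** Because the vignettes differ between time points, "within-person analyses will be conducted on participant-level summary indices". The methods then divide by arm: "For the No-C-SSRS condition, paired non-parametric tests, such as the Wilcoxon signed-rank test, and correlation analyses will be used"; and "For the C-SSRS condition, indices of temporal consistency will be computed to evaluate the stability of" participants' general classification tendency.
- **Mixed model (2.5.2).** "Fixed effects will include study group, experimental condition (C-SSRS vs. No-C-SSRS), time (baseline vs. follow-up), and their interactions". On random effects: "Random intercepts will be specified for participants to account for repeated ratings within individuals", and for vignettes where appropriate. No arm-specific within-person variance is mentioned.

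**The concern.** HP5 is a statement about a difference between two randomised arms, so it needs one quantity measured the same way in both arms and a contrast of that quantity. The plan instead gives a signed-rank p-value and a correlation on 1–9 summaries in one arm, and an unspecified index on categories in the other. These results share no scale and cannot be subtracted.

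The No-C-SSRS statistics also do not all address agreement. A signed-rank test looks for a systematic shift between baseline and follow-up. People can vary widely in both directions and still give a null result.

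At stake is any conclusion that the C-SSRS did or did not improve within-person consistency. Setting two within-arm results side by side gives no effect estimate, interval or error rate. It also mixes the effect of the response format with the effect of the randomised condition.

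**Working it through.** **1. The plan's own figures reproduce.**
- Sample size (2.5.1): one-way ANOVA, 10 groups, f = 0.20, two-sided alpha 0.05, power 0.80. With noncentrality N × f², N = 400 gives 400 × 0.04 = 16 on 9 and 390 degrees of freedom. Power is 0.8003, and 400 is the smallest N reaching 0.80.
- Follow-up (2.5.1): 500 × 0.55 = 275 and 500 × 0.60 = 300.

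Neither figure concerns a between-arm comparison of consistency, for which the plan states none.

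**2. What condition by time measures.** Suppose that in one arm half the participants move up one category and half move down one, while in the other arm nobody moves.
- Mean change: 0.5 × (+1) + 0.5 × (−1) = 0 in the first arm and 0 in the second. The condition-by-time contrast of level is 0, and a signed-rank test in the first arm has no shift to find.
- Mean absolute change: 1 in the first arm and 0 in the second. This is the difference that HP5 is about.

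**3. Simulation (illustrative).** The latent-scale settings are assumptions, not document figures: participant SD 0.6, residual SD 0.8, designed levels at −2, 0 and 2, category cut points at −1 and 1. There were 2,000 runs per setting, with 138 or 150 completers per arm and two vignettes per risk level at each time. Condition by time was approximated by a two-sample t-test on change in mean category. The common index was the absolute change in mean category within each risk level, averaged over the three levels and compared by a Mann–Whitney test.

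| Person-by-time SD, No-C-SSRS / C-SSRS | n per arm | Condition by time | Wilcoxon within No-C-SSRS | Common index between arms |
|---|---|---|---|---|
| 0.8 / 0.3 (consistency differs) | 138 | 4.4% | 4.8% | 99.1% |
| 0.8 / 0.3 | 150 | 4.7% | 4.3% | 98.7% |
| 0.5 / 0.5 (consistency equal) | 138 | 4.4% | 4.7% | 4.9% |
| 0.5 / 0.5 | 150 | 5.7% | 4.6% | 4.7% |

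When only consistency differs, the first two statistics reject at about the nominal 5%.

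**4. Effect of format alone.** With equal true consistency in both arms, the baseline-to-follow-up correlation averaged about 0.61 on the 1–9 scale and about 0.50 on three categories. Under these settings an informal comparison would make the C-SSRS arm look less stable because of its response format.

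**5. What a common index could detect.** Assuming a 1:1 split, 275–300 completers give 137.5–150 per arm. The standardised difference detectable at 80% power, two-sided 5%, is (1.960 + 0.842) × √(2/n):
- n = 137.5: 2.802 × 0.1206 = 0.338
- n = 150: 2.802 × 0.1155 = 0.323

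**The case against.** **The plan does compare the arms over time.** A reader might infer that no planned test takes both arms. The document does not support that. Condition by time, and its interaction with study group, are randomised contrasts using both arms, and 2.5.2 describes the within-person target as including participants' overall level. Differential drift in average level is therefore covered. What is not covered is how consistent individuals are.

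**The ingredients of a common index are present.** A reader might also infer that the within-person analyses ignore the three categories. That is not established. Before splitting by arm, 2.5.2 gives the distribution of risk categories as an example of a summary index, and 2.4.2 introduces Table 1 to allow comparison of the conditions. What is missing is a stated contrast between arms.

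**Detail may sit in a fuller plan.** The wording is illustrative and the C-SSRS indices are unnamed; naming an index can fairly be left to an analysis plan. But the article goes further than leaving detail open: it assigns different methods to the two arms for a hypothesis that compares them. An analysis plan that followed it would inherit the problem.

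**The arms differ by design.** Section 2.3.1 defends the two response formats as distinct assessment paradigms. That justifies collecting different ratings. It does not supply a test of HP5, which presupposes a comparable measure.

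**The remedy has weaknesses of its own.** These stand. Collapsing 1–9 to three bins depends on cut points that 2.5.2 itself treats as a possible source of bias. With two vignettes per level, each level mean takes only five values, and different vignettes at each time add noise. A rater who always answers moderate scores as perfectly consistent. Follow-up depends on a voluntary e-mail address, with 40–45% attrition assumed, so a completer comparison is not a clean randomised contrast.

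**Effect size.** It is tempting to convert f = 0.20 to d = 0.40 and call the comparison well powered at the plan's effect size. That f refers to baseline ratings across ten groups and does not carry over to a two-arm consistency index.

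**Conclusion.** The concern holds in a bounded form. As written, the within-subject clause of HP5 has no between-arm test: the arm-specific analyses are not comparable, and condition by time with random intercepts only addresses average level. This affects one clause of one hypothesis under Aim 3. It does not touch the comparison of study groups or the between-subjects clause of HP5.

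The conclusion about the methods follows from the text and needs no simulation. The rejection rates and correlations rest on assumed latent SDs and cut points and only illustrate the mechanism. The detectable difference of about 0.32–0.34 rests on 275–300 completers split 1:1. It shows what a common index could detect, and is not a shortfall in a planned test.

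**What to change.** In 2.5.2, for the within-subject clause of HP5:

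1. Define one participant-level consistency index on the Table 1 categories, computed identically in both arms. One example is the absolute baseline-to-follow-up difference in mean category within each designed risk level, averaged over the three levels.
2. Compare it between conditions with study group in the model, and report the difference with a confidence interval. A model with arm-specific within-person variance is an alternative.
3. Repeat it under the alternative binning already planned (such as 1–2, 3–7, 8–9).
4. Report it alongside agreement with the designed risk level, so that a constant moderate rater is not read as a good one.
5. Keep the 1–9 Wilcoxon and correlation results as descriptive for the No-C-SSRS arm.
6. State that the contrast is among self-selected follow-up completers, and report completion by arm.

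The cost is analysis-plan wording: the ratings and conversion table already exist. The downsides are lost 1–9 detail in this one comparison and dependence on the cut points, which step 3 shows but does not remove.
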